## Methods/Design

### Study design

The study is a cluster RCT (Fig. 1) delivered within the context of the existing Go4Fun program with 10 week, 6 month, and 12 month follow-up (*n* = 40 sites, 570 participants), which compares the effectiveness of participation in the standard Go4Fun program with an enhanced goal setting and structured incentive scheme (intervention) versus participation in the existing Go4Fun program (control). Individual randomization is not possible given the nature of the intervention, so randomization by site will be conducted. Building on our existing research platform, we propose a pragmatic and feasible trial to determine the effectiveness, acceptability, and sustainability of the enhanced intervention at 6 and 12 months after the program. The CONSORT statements for cluster RCTs [43] and for nonpharmacological interventions [44] will be followed.

**Fig. 1 Fig1:**
[figure not shown]
Behavioral incentive study schema. BMI, body mass index; QOL, quality of life

### Eligibility/recruitment: Sites (namely programs where Go4Fun is delivered)

To be eligible to participate in the trial, sites must meet the following criteria:Are delivering the standard Go4Fun program in 2015;Show a 2014 attendance average of at least 10 children enrolled per program per term; andAre willing to participate in a trial and adhere to standardized procedures for the duration of the trial.

For site recruitment, all NSW LHDs (where Go4Fun is delivered) were invited to participate, 40 programs agreed to participate, and ethical approval was secured from the relevant LHDs. Based on prior process evaluation work [17] and from prior attendance records, the recruited sites are likely to enroll an average of 12 to 15 children per site per term. Local program leaders will assess eligibility, obtain informed consent, and conduct baseline study visits, and research assistants will conduct the follow-up assessments. Previous RCTs conducted by the research team have underscored the critical importance of site-based program leader involvement and engagement to maximize downstream sustainability.

### Eligibility/recruitment: Participants

To be eligible to participate in this trial, leaders were instructed that children must meet the following criteria:i.Aged 7 to 13 years;ii.Have a body mass index > 85th percentile for their age and sex (according to AIHW classification of overweight/obesity in children) [19, 45];iii.Be enrolled in and meet the general criteria to participate in the Go4Fun program at one of the sites participating in this study, which includes having a parent or adult carer able to accompany them to each session; andiv.Parent/guardian provides written and informed consent.

Participant/child eligibility for the Go4Fun program is assessed at the time of referral/contact with their LHD. No changes will be made to this standard program enrolment process. Eligibility will be determined by the program leaders based on assessment of the above criteria once the child attends the initial intake appointment, and written informed consent will be sought prior to collection of baseline data.

### Randomization

Eligible sites have been randomized to either deliver the intervention (standard Go4Fun plus incentives) or control (standard Go4Fun) program for 10 weeks. Randomization was conducted using a computer-generated sequence (1:1) managed by the research team based at The George Institute and independent of the Department of Premier and Cabinet NSW (DPC), any program leader or LHD. Clusters were stratified according to local health district to ensure equal representation across groups within each LHD.

### Development of incentive scheme and standardized program

In late 2014, an iterative process combining literature review, focus groups, and consensus meetings took place with three aims: namely, to (i) identify the best possible incentive scheme based on available literature, (ii) standardize the existing Go4Fun attendance rewards system across all treatment and control sites, and (iii) develop and agree on the goal setting scheme and incentive structure to be used for the intervention group. Participants included representatives from authorship group, program leaders representing all LHDs, DPC (the Government department responsible for delivery of Government priorities in NSW, Australia), Better Health Company, and the NSW Office of Preventive Health. In addition, investigators from DPC conducted six field research visits (including interviews) to collect feedback and ideas from the Go4Fun leaders about potential ways to enhance the goal setting process and practical considerations regarding delivery and impact as well as post-program engagement opportunities. A literature review demonstrated the importance of incentivizing behavior rather than outcomes. This approach was confirmed by Go4Fun leaders during early fieldwork so that, despite being a core part of the Go4Fun program, goal-setting structures could be improved by making the goals specific, measureable, achievable, relevant, and timely (SMART) [32]. This emphasized the importance of enhancing the goal-setting process, including resetting/stretching them if they are achieved too easily in the program, as well as linking goal achievement to incentives [32].

Preliminary work highlighted the need for a standardized reward system for the control program, and “healthy,” positive, and low-cost incentives (for example, items that encourage physical activity and nutrition) were needed for the intervention group. It was also agreed that incentives should be of increasing value as they become harder to achieve. Once consensus was reached regarding the control program and the incentive scheme for the intervention, formal standard operating procedures were prepared and circulated for revision and refinement until consensus was reached. This process was important to facilitate engagement and satisfaction of site leaders and to minimize potential variability between sites. Specific rewards and associated delivery structure are outlined further in the “intervention” section of this proposal.

### Control group

Sites randomly allocated to the control group will continue to deliver the standard Go4Fun program. As described above, the standard program consists of weekly group sessions (one per week) for 10 weeks during the school term. Exercise sessions involve one hour of activities that progressively develop skills, strength, fitness, confidence and self-esteem [17]. Nutrition sessions include healthy eating advice, food label reading and recipes [17]. Behavioral change sessions include goal setting, problem solving and role modelling to influence habits and behavior around eating and exercise [17]. Through preliminary focus groups, consensus was reached to ensure the standardization of Go4Fun between sites. In particular, when and how children receive reward “stickers” was standardized throughout the control program. It was also agreed that children would receive incentives such as water bottles (for attending one session), bouncy balls (for attending three sessions), and skipping ropes (for attending 10 sessions) based on their record of attendance.

### Intervention group

Sites randomly allocated to the intervention arm will deliver the Go4Fun program with the enhanced goal setting and structured incentive scheme developed during our preliminary work. As described above, the standard program consists of weekly group sessions (one per week) for 10 weeks during the school term. No sessions have been lengthened or combined for the intervention sites. All children participating in the intervention sites will receive the same information and participate in the same exercise and nutrition sessions as the control group. They will also receive the same system of “reward stickers” and standardized attendance rewards throughout the program. However, at intervention sites, participating children will be eligible to participate in an enhanced goal-setting component and receive incentives for reaching certain levels of goal attainment. That is, for the intervention, participants will set SMART [32] behavioral goals and achieving these goals will result in the incentives being provided. This emphasizes the importance of enhancing the goal-setting process, including resetting/stretching them if they are achieved too easily in the program, as well as linking goal achievement to incentives [32]. The incentives will only be received for the period of the 10-week program.

The goal setting component and incentive scheme was developed and agreed upon during the preliminary work for this study with an overview of the goal setting enhancement and incentives being as follows:*Goal setting:* At the third session in the program, the children and their parent/ guardian in the intervention group are provided with an enhanced resource to guide them through jointly setting an exercise and a nutrition goal (child and parent/guardian in collaboration). Examples include ‘I will play soccer for 30 minutes on 3 days a week at the park with dad’ and ‘I will try a new vegetable two times a week for dinner on Wednesday and Sunday nights.’*Goal attainment incentives:* Children will receive milestone-based incentives for achieving their set goals. There will be three levels as follows: (i) a vegetable slicer once two exercise and two nutrition goals are achieved; (ii) a sports store voucher (value of $AUS10) once four exercise and four nutrition goals are achieved, and (iii) a height-adjustable tennis set once six exercise and six nutrition goals are achieved. In addition, Go4Fun leaders will ask the children on a weekly basis if they have achieved their goal and prompt them to reset them if they were too easy.*Goal attainment reminders via text message and lottery style incentive:* After the 10-week program, parents/ guardians will receive weekly mobile phone text message reminders to support and encourage children to achieve their goals (and set new ones where relevant). Parents/ guardians will be encouraged to text back with goal achievements with each goal achieved being rewarded with a ticket entry (maximum of eight tickets per month) into a prize draw (one per program) for a family pass to a local zoo (or similar family activity, depending on local availability) that will be drawn at 6 months.

### Outcomes

Data will be collected for all participants at baseline, end of program, at 6 months, and 12 months. The primary outcome is a mean change in BMI *z* score at 12-month follow-up. BMI *z* scores indicate how many units (of the standard deviation) a child’s BMI is above or below the average BMI value for their age and sex. BMI *z* scores will be calculated from raw BMI measures using the Centers for Disease Control growth reference data [46]. Secondary outcomes include anthropometric measures (body weight, height, and waist circumference) assessed according to standardized procedures [47] and behavioral measures collected via validated questionnaires (Table 1). Similar to the BMI *z* scores, waist measures in centimeters will be converted to a waist circumference *z* score based on reference data [46]. The Physical Activity Enjoyment Scale (PACES) will be used to assess physical activity, and this tool has been found to have good internal consistency, item-total correlations, and validity in primary school children (*n* = 564) [48]. Scores were also correlated with task goal orientation, athletic competence, physical appearance and self-reported physical activity [48]. For nutrition questions, we selected relevant questions from the NSW Centre for Public Health Nutrition recommendations for nutrition questions [49]. These questions are recommended for practical assessment and have been developed based on evidence and guidelines for children [49]. An adapted version of the Rosenberg Self-Esteem Scale will be used and is one of the most widely used self-esteem measures in social science research [50]. This scale has been tested for reliability and validity in many languages and has been found to be effective including in children [50].

**Table 1 Tab1:** Primary and secondary outcomes (measured at baseline, end of program, 6 months, and 12 months)

Primary
• Mean change in BMI *z* score* (measured using standardized procedures [47]) at the end of the program (10 weeks) and at the 6-month and 12-month follow-up
Secondary (measured at the end of the program and at the 6-month and 12-month follow-up)
• Mean change in mean waist circumference and waist *z* score, measured using standardized procedures [47]
• Mean change in mean BMI* - measured using standardized procedures [47]
• Difference in mean rate of goal attainment between intervention and control groups for nutrition and physical activity – child diaries verified by parent/guardian
• Mean difference in physical activity level – Physical Activity Enjoyment Scale (PACES) [48]
• Difference in fruit and vegetable, breads and cereals and dairy intake per day; fast food and sweetened drink intake per week - based on NSW Centre for Public Health Nutrition recommendations for nutrition questions [49]
• Mean difference self-esteem – Rosenberg Self-esteem Scale [50]

*BMI (kg/m^2^) calculated based on the measurement of height and weight using standardized procedures [47] and BMI *z* score calculated based on Centers for Disease Control reference data [46]

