In summary, early research suggests that the use of incentives for promoting behavior change in overweight/obese children has potential, but to date, this is a relatively unexplored area. The overall objective of this research is to apply behavioral insights to determine the effectiveness of a structured goal setting and incentive scheme to improve health-related behaviors in overweight/obese children. The opportunity also exists to test, using text message reminders and lottery prize draw, whether any gains made during the program are maintained and whether the effects of incentives are sustained after the program, as a cost-effective way of engaging with families after the program. The specific aims of this research are as follows:To determine the effectiveness of a structured goal setting incentive scheme on the following:i.Health outcomes (body mass index (BMI) and waist *z* scores, BMI, waist circumference, nutrition, physical activity, and self-esteem) at the end of the program (10 weeks), 6 months, and 12 months;ii.Completion of at least 75 % of the Go4Fun weight management program and;iii.Achievement of physical activity and nutrition goals during the Go4Fun program.To determine the effectiveness of post program text message reminders highlighting a lottery prize draw on the following:i.Sustained health outcomes (BMI and waist *z* scores, BMI, waist circumference, nutrition, physical activity, and self-esteem) at 6 months, and 12 months after the program; andii.Achievement of physical activity and nutrition goals at the end of the program (10 weeks), 6 months, and 12 months after the program.To determine the acceptability (via a process evaluation) of the structured incentive scheme to inform widespread policy translation and implementation.

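### The secondary outcome labelled physical activity level is measured with PACES, an enjoyment scale, so it cannot support a between-group conclusion on amount of activity

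*Protocol article*

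**What the plan says.** Three places in the protocol article fix this outcome.

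- **Table 1 (Outcomes)** gives the construct and its instrument in one row: "Mean difference in physical activity level – Physical Activity Enjoyment Scale (PACES"). No other instrument is named in that row.
- **The Outcomes text** repeats the link: "The Physical Activity Enjoyment Scale (PACES) will be used to assess physical activity". It supports the choice with internal consistency, item-total correlations and validity in primary school children, and adds: "Scores were also correlated with task goal orientation, athletic competence, physical appearance and self-reported physical activity".
- **The aims**, at the end of the Background, list physical activity among the health outcomes. Aim 1 covers "waist circumference, nutrition, physical activity, and self-esteem) at the end of the program (10 weeks), 6 months, and 12 months". Aim 2 covers the same health outcomes at 6 and 12 months.

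Table 1 has one further row that touches activity: "Difference in mean rate of goal attainment between intervention and control groups for nutrition and physical activity – child diaries verified by parent/guardian". It serves aims of its own, such as "Achievement of physical activity and nutrition goals during the Go4Fun program".

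**The concern.** The row names one construct and measures another. How active a child is and how much the child enjoys activity are different quantities, and a trial of rewards is a setting in which they may part. The intervention pays children, in goods and vouchers, for meeting exercise goals. Activity could rise because it is rewarded while enjoyment stays flat or falls. Enjoyment could also rise without any change in activity.

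If the PACES result is reported under its present label, a null result would be read as no effect on activity, and a positive one as more activity. Neither reading follows from an enjoyment score. The Discussion says that the study will inform policy and program delivery, so the label would carry the wrong construct to the readers whom the trial is meant to serve.

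**Working it through.** No figure in the plan is in dispute, so the check sets the statements side by side.

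**1. Does the article equate PACES with activity or separate the two?** It does both. One sentence says that PACES will assess physical activity. Shortly afterwards, PACES scores are said to correlate with four other variables, one of which is self-reported physical activity. A score that correlates with reported activity is not a report of activity. The same list contains athletic competence and physical appearance, and nobody would relabel PACES as a measure of either.

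**2. Could the correlation carry the inference?** The article gives no coefficient. For illustration only, an assumed r of 0.2 to 0.5 gives shared variance r² from 0.2² = 4% to 0.5² = 25%. The conclusion does not rest on this range. Even a strong correlation between children would not make an arm difference in one variable an arm difference in the other, because the intervention may change the relation between them.

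**3. How are neighboring outcomes specified?** The nutrition row in Table 1 is expressed as intake per day or per week. The activity row has no comparable quantity: no minutes, days, frequency or intensity. The Outcomes and Data collection sections name no activity monitor and no questionnaire on amount of activity.

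**4. Does the diary row fill the gap?** It is relevant, because an activity goal can state duration and frequency. The article's own example is "I will play soccer for 30 minutes on 3 days a week at the park with dad", that is 30 × 3 = 90 minutes a week. Three features stop attainment from being a common scale of level:

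- *Goals are individual.* Parent and child set them jointly, so the same attainment rate can stand for different amounts of activity.
- *Goals move.* In the Intervention group section, leaders ask weekly about achievement and "prompt them to reset them if they were too easy". A child who met the 90-minute goal, was given a harder one, and then did more than 90 minutes but missed the new target would show lower attainment with higher activity.
- *The arms differ in the process that generates the measure.* Control sessions include goal setting. The enhanced resource, the goal-linked incentives, and the later text messages with prize-draw entries are described for the intervention arm only. Attainment is therefore supported and rewarded in one arm and not in the same way in the other.

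**5. Which aims and visits are affected?** Aim 1 at three follow-up times (10 weeks, 6 and 12 months) and aim 2 at two (6 and 12 months), for the physical activity component only.

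**The case against.** The best reply is that the trial does collect information on activity behavior. The goal-attainment row stands in the same table, is recorded in child diaries, is verified by a parent or guardian, and is planned for end of program, 6 and 12 months. A reader might infer from the PACES row that the trial can say nothing at all about how active the children were, or that no listed outcome touches frequency or duration. The document does not support that reading. Goals may specify minutes and days, and attaining them is evidence on behavior. What remains of the concern is that attainment is not a level that can be compared between arms.

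A second reply is that PACES is reported to have good measurement properties in primary school children. That stands too. The point is not that PACES is a poor scale, and the document gives no basis for saying how weakly it tracks activity. The point is that validity as an enjoyment scale does not license the label activity level.

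A third reply is that this is one secondary outcome and that correct labelling removes the harm. That is true, and it is why the remedy is small.

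**Conclusion.** The point holds in this form: the outcome called physical activity level is defined by an enjoyment scale, and a PACES difference cannot support a between-group conclusion on amount of activity under aims 1 and 2. Diary-based goal attainment bears on activity behavior but does not supply a measure of level.

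Confidence is high on the mismatch of label and instrument, which rests on the article's own words and on no outside source. The numerical size of any resulting error cannot be derived, because neither a coefficient nor an activity measure is given. The consequence is confined to one secondary outcome. The primary outcome, BMI z score at 12 months, its sample size and its analysis are not touched.

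**What to change.** Rename the Table 1 row to *physical activity enjoyment (PACES score)*, make the same change in the Outcomes sentence that says PACES assesses physical activity, and align the physical activity wording in aims 1 and 2. State that no conclusion on activity level will be drawn from PACES. Report diary goal attainment under its own aims, as attainment and not as amount of activity.

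The cost is wording, plus one fewer behavioral claim. The Trial status section says that no data cleaning or analysis had begun, so the change could be made without knowledge of results.

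An activity-level outcome should be kept only if the program is confirmed to record an item on amount of activity in both arms; that item would then be the outcome. The document does not show that one exists. The Background reports earlier program improvements in physical activity but does not name the instrument, which could itself be PACES. Recruitment had already started, so an instrument added now would lack baseline values for children already enrolled.

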### Data collection

Data will be collected at baseline, end of program, 6 months, and 12 months by research assistants. For baseline measures, staff members have been trained by the Better Health Company investigator team in measuring height, weight, and waist circumference using standardized procedures [47]. All participants will be contacted to attend the follow-up sessions, and they will be incentivized with a gift voucher (value of $AUS25) for attending each of the 6- and 12-month health checks These payments are to maximize the rate of follow-up for the research study and are offered to both control and intervention site participants. Data will be entered into a secure online database that will require minor additional functionality for the collection of goal attainment and 6- and 12-month follow-up data.

